### Study design and setting

The study will be carried out in three German federal states that are covered by the RESPoNsE network (Berlin, Brandenburg, and Thuringia), comprising approximately eight million inhabitants.

Due to the explorative nature of the study, no sample size calculation was undertaken. Every GP in Berlin and Brandenburg who is statutory health insurance registered (approximately n = 4.100) may take part in the study. The response rate will be a secondary outcome, comparing the rates for GPs who already are part of the RESPoNsE network with those who are not. As other surveys in the Thuringia GP practices are taking place at the same time, only those practices that already are members of RESPoNsE (n = 70) are invited to take part in the study. There are no exclusion criteria.

The GPs have received a postal invitation to take part in the study. MPAs may take part in the study independently of the GPs in the same practice but, as we only have information on the GPs working per practice (and not the MPAs), MPAs will only receive information about the study from the GP who received the letter at their practice.

In line with previous work and similar surveys with GPs, we expect a response rate of about 25% [56, 57]. We expect the response rate to be higher among GPs who are already a part of the RESPoNsE network. As we don`t know how many MPAs are working in the practices we will not be able to calculate a response rate for the MPAs.

The letter to the GPs consists of:

a study information;the questionnaire for GPs (to be filled out anonymously);the questionnaire for MPAs (to be handed out to interested MPAs in the same practice and filled out anonymously by as many MPAs as are willing to take part in the study—the questionnaire be copied if necessary);a prepaid return envelope;a response form (S1 Form), asking for their readiness to take part in the survey or in the further portions of the study (to be filled out with contact details and to be sent back separately via fax or mail);The GPs and MPAs in Berlin and Brandenburg who are not yet members of the RESPoNsE network are also provided with information on network activities and aims and will be asked to express their interest to be part of the network.

After 4 weeks the same letter was sent as a reminder to those GPs who had not yet returned their response form (Fig 1).

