	Requirements/resources in order to maintain health care provision during the pandemic (for example, material, qualification, information).	strongly agree–agree—neutral- disagree -strongly disagree
	*Example statement*: *“In order to maintain the provision of care under pandemic condition we need … better qualified personnel”*	
GPs only	Subjective assessment of usefulness of information by different professional associations and organizations during the pandemic (for example, the General Medical Council, Standing Committee on Vaccination, Federal Centre for Health Education, German College of General Practitioners and Family Physicians).	Very helpful–rather helpful–neutral–rather not helpful–not helpful at all –don´t know
	*Example statement*: *“How would you assess the information given during the pandemic by the… German College of General Practitioners and Family Physicians“*	
MPAs only	Personal anxieties and concerns during the pandemic (for example, stress, risk of infection and health issues, social conflicts, economical burdens).	strongly agree–agree -neutral- disagree -strongly disagree
	*Example statement*: *“What are the primary issues of fears and worries for you during the pandemic… constant stress “*	

Participating GPs and MPAs will be asked to fill in a second questionnaire after 12 to 18 months. In this way, we will explore which views and possible changes in health services persist over time. As the questionnaires will be anonymous, the comparison will be made on an aggregated level.

The GPs who participated in the first survey will also be asked to cooperate in the patient survey. Those who indicate an interest on the response form will be contacted again with further information on the proceedings and will be asked to consent into participating in the study. From a previous study (not yet published), we expect about 50 to 100 GPs to take part in this portion of the study. Participating GPs may indicate whether they expect to successfully distribute questionnaires for 50 or 100 patients during the standardized study period of four weeks. Questionnaires will be sent to the practices accordingly to be distributed among patients who sit in the waiting room. Patients will be provided with information on the study, asked to fill in the questionnaire anonymously, and to place it in a pre-prepared box. After the given study period, the practice team will send back the questionnaires using a prepaid envelope.

Inclusion criteria are:

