### Outcomes

The primary outcome is that the views of GPs, MPAs, and patients be obtained, on the supply and utilization of health services during the COVID-19 pandemic, addressing positive as well as negative aspects, such as:

aspects of underutilization/undersupply;possible identification of services that turned out not to be necessary;unanticipated benefits like improvement of organizational matters and use of virtually-delivered care.

Piloting the structural development of the network, secondary outcomes are the number of participating GPs and MPAs and the number of participating patients. The number of participating GPs will be compared in terms of whether or not they are members of RESPoNsE.

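### The reminder was triggered by a missing response form, not a missing questionnaire, so GPs who had already answered anonymously could be mailed again and counted twice

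*Protocol article*

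**What the plan says.** All the elements of the mailing are in the Protocol article under Study design and setting.

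- The letter contains "the questionnaire for GPs (to be filled out anonymously").
- It also contains an MPA questionnaire, "filled out anonymously by as many MPAs as are willing to take part in the study—the questionnaire be copied if necessary".
- It contains a response form "asking for their readiness to take part in the survey or in the further portions of the study". This form is "to be filled out with contact details and to be sent back separately via fax or mail".
- The reminder rule is: "After 4 weeks the same letter was sent as a reminder to those GPs who had not yet returned their response form".

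Under Quantitatively: Surveys, the two survey waves cannot be linked by person: "As the questionnaires will be anonymous, the comparison will be made on an aggregated level".

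Study design and setting makes the GP response rate, compared between network members and non-members, a secondary outcome. Outcomes adds that "secondary outcomes are the number of participating GPs and MPAs and the number of participating patients".

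**The concern.** The reminder depends on one document (the identified form), while the survey data come from another (the anonymous questionnaire). The two need not be returned together. A GP content to answer anonymously has little reason to send back a form that gives contact details and asks about further parts of the study. Such a GP looks like a non-responder at four weeks and receives a fresh GP questionnaire and a fresh MPA questionnaire to hand out.

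If some of these people complete the questionnaire again, three things are affected. The numbers of participating GPs and MPAs are too high. The GP response rate is too high if its numerator is questionnaires. The chi-square and other tests in Data analysis treat two records from one person as independent, though this effect is smaller. If members and non-members return the form at different rates, the excess could also differ between the two groups being compared.

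The trigger fails in the other direction as well: a GP who returned the form but not the questionnaire received no reminder.

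**Working it through.** **Step 1: who was mailed again.** The four combinations at four weeks, under the stated rule:

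| Questionnaire returned | Form returned | Reminder with full set? |
|---|---|---|
| yes | yes | no |
| yes | no | **yes, although already answered** |
| no | yes | **no, although not answered** |
| no | no | yes |

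The rule misdirects the reminder in the second and third rows. The second row creates the opportunity for a duplicate.

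**Step 2: is there a safeguard?** The article describes no respondent code, no request to disregard the reminder, no marking of the second mailing and no duplicate check. Data analysis mentions data cleaning without detail.

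**Step 3: size.** The article gives no expected number of returns or duplicates to reproduce. Two inputs are stated in Study design and setting: about 4,100 eligible GPs in Berlin and Brandenburg and an expected response of about 25%.

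Expected returns: R = 0.25 × 4,100 = 1,025.

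Three shares are **not** in the document and are assumed:
- a = share of respondents answering before the reminder (50% to 70%)
- b = share of those who sent no form (20% to 80%)
- c = share of those who answer again (2% to 20%)

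Unneeded second sets = R × a × b. Duplicates D = R × a × b × c. Share of returns that are duplicates = D / (R + D). Counted rate = (R + D) / 4,100.

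| Case | a, b, c | Unneeded sets | D | D / (R + D) | Counted rate |
|---|---|---|---|---|---|
| Low | 50%, 20%, 2% | 102 | 2 | 0.2% | 25.05% |
| Middle | 50%, 50%, 5% | 256 | 13 | 1.2% | 25.3% |
| High | 70%, 80%, 20% | 574 | 115 | 10.1% | 27.8% |

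Middle case in full: 1,025 × 0.5 × 0.5 × 0.05 = 12.8; 12.8 / 1,037.8 = 1.2%; 1,037.8 / 4,100 = 25.3%.

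Adding the 70 Thuringia practices as one GP each (an assumption) gives 0.25 × 4,170 = 1,042.5 expected returns, and the percentages do not change.

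MPA duplicates come on top. They cannot be sized, because the number of MPAs in the practices is unknown. For the same reason an excess of MPA questionnaires could not be noticed.

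**Step 4: does the response rate depend on questionnaires?** The article does not say which return is counted. The questionnaire items listed under Quantitatively: Surveys are gender, age, location of practice and professional experience; network membership is not among them. The comparison of members with non-members may therefore rest on the identified forms. In that case repeat questionnaires would not inflate it, but GPs who answered without sending the form would be missed.

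**The case against.** The best case on the other side has five parts.

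- **Unseen material.** The cover letter, the response form (S1 Form) and the flow chart are not shown. Any of them could ask earlier respondents to ignore the reminder, and the form may be meant as a reply card for everyone. This stands as a possibility. It would settle the point in one sentence, but the procedure as described contains no such step.
- **Response rate.** A reader might infer that the published response rate is necessarily inflated. The document does not support this, because the rate may be counted from forms. The participant counts remain exposed wherever they rest on questionnaires.
- **Size.** A reader might take the 10% figure as an estimate. It is not one: it comes from setting all three assumed shares at their upper ends. Someone must fill in the same questionnaire twice, in practices that the article itself describes as overburdened, so a small number is more plausible.
- **MPAs.** Permission to copy the questionnaire might be read as a source of duplicates. It only lets several MPAs answer. Receiving a set through more than one GP in the practice is possible, but Box 1 says German GPs largely work single-handed, which limits that route.
- **Primary outcome.** It is a descriptive account of views in an exploratory study. Repeat answers of about 1% would hardly move the reported proportions. This stands.

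**Conclusion.** The point holds as a flaw in a stated rule: the reminder went by the wrong return and re-sent the full questionnaire set, and nothing described prevents or detects a second completion. The document shows that people **could** be counted twice; it does not show that any were.

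The exposed quantities are the participant counts and, if it is counted from questionnaires, the GP response rate. The effect on the primary descriptive results is minor. The size is probably small: about 1% of GP returns and 0.3 percentage points on a 25% rate under moderate assumptions, and about 10% and 2.8 points only under extreme ones. These figures rest on three assumed shares that the document does not give.

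**What to change.** **Wave 1 (already mailed): reporting only.**
- State whether the response rate and the comparison of members with non-members are counted from forms or from questionnaires.
- Where receipt dates exist, report questionnaires received before and after the reminder separately.
- With respect to duplication, present a questionnaire-based response rate as an upper bound.
- Use an analysis limited to returns before the reminder only as a rough check. It also drops genuine late responders, so any difference mixes duplication with early versus late response.
- Do not rely on searching for identical answer patterns: a person who changes one answer the second time is missed.

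**2023 wave, if a reminder is sent.**
- Print on the GP and MPA questionnaires: *If you have already completed this questionnaire, please do not fill it in again.*
- Mark the reminder questionnaires so that the two mailings can be told apart.
- Add a box to the separate response form, unless it is already there: *I have returned the questionnaire.* Use that box, rather than return of the form as such, to decide who gets the reminder. This also reaches GPs who sent the form but not the questionnaire.

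Anonymity is kept throughout. The cost is a printed line, a mark on the reminder forms, a tick box and a short data check. The stated response rate may turn out slightly lower.

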**Fig 1 pone.0279413.g001:**
[figure not shown]
Flow chart of participants.

### Study structure

This convergent mixed methods study includes the following methodological approaches (see Table 2 for a summary):

**Table 2 pone.0279413.t002:** Study structure: Purpose and data source.

	Purpose	Data Source
Phase 1 Participatory approach	Collect themes for surveys. Develop surveys.	Practice advisory board. Patient advisory board.
Phase 2 Surveys with GPs, MPAs and patients	Explore experiences of the three groups during the COVID-19 pandemic. Recruit MPAs and GPs for interviews. Recruit GPs and MPAs for the PBRN.	GP and MPAs in three federal states. Patients of participating GP practices.
Phase 3 Qualitative interviews	In-depth exploration of survey results.	GPs and MPAs in three federal states.
Phase 4 Follow-Up Surveys	Repeat survey (GPs and MPAs) to explore views and attitudes one year later.	GPs and MPAs who took part in the first survey.

### Quantitatively: Surveys

The questionnaire for GPs and MPAs was constructed and piloted with the participation of the practice advisory board and addresses aspects of routine health care provision during the COVID-19 pandemic, as well as organizational, technical, and staffing measures, external information, and fears and worries about their work environment during the pandemic.

Most of the questions are the same or equivalent for both GPs and MPAs, including information on demographic and professional characteristics (gender, age, location of practice, professional experience). One thematic block varies between the two groups, allowing for a different focus during the preparatory discussions in the meetings with GPs and MPAs. Except for the demographic questions, all the other items are designed on a five-point Likert scale, supplemented by a “don´t know” category where appropriate (Table 3; S2 and S3 Files).

**Table 3 pone.0279413.t003:** Questionnaire for GPs and MPAs (themes, examples, scale).

	Thematic block	Scale
Identical / equivalent to GPs and MPAs	demographic and professional characteristics (gender, age, location of practice, professional experience)	Single choice items
	Changes in frequency for procedures during the coronavirus pandemic (for example scheduled / unscheduled visits, virtually delivered care by use of video or telephone, home visits, routine checks, vaccinations other than Covid-19)	Much less frequent–less frequent–no change–more frequent–much more frequent–don´t know
	*Example statement*: *“How has the frequency for the following service for non-Covid-19 related conditions changed during the pandemic … home visits”*	
	Subjective assessment of the quality of care for chronically ill patients during the corona virus pandemic (for example, changes in quality of care, changes in health conditions of the patients, changes in number of practice visits).	strongly agree–agree—neutral- disagree -strongly disagree -don´t know
	*Example statement*: *“We managed to provide the same quality of care as before”*	
	Personal view on working conditions and job satisfaction during the pandemic (for example, expectations, conflicts within the team, joy at work).	strongly agree–agree—neutral- disagree -strongly disagree
	*Example statement*: *“I am thinking about changing my job”*	
	Requirements/resources in order to maintain health care provision during the pandemic (for example, material, qualification, information).	strongly agree–agree—neutral- disagree -strongly disagree
	*Example statement*: *“In order to maintain the provision of care under pandemic condition we need … better qualified personnel”*	
GPs only	Subjective assessment of usefulness of information by different professional associations and organizations during the pandemic (for example, the General Medical Council, Standing Committee on Vaccination, Federal Centre for Health Education, German College of General Practitioners and Family Physicians).	Very helpful–rather helpful–neutral–rather not helpful–not helpful at all –don´t know
	*Example statement*: *“How would you assess the information given during the pandemic by the… German College of General Practitioners and Family Physicians“*	
MPAs only	Personal anxieties and concerns during the pandemic (for example, stress, risk of infection and health issues, social conflicts, economical burdens).	strongly agree–agree -neutral- disagree -strongly disagree
	*Example statement*: *“What are the primary issues of fears and worries for you during the pandemic… constant stress “*	

Participating GPs and MPAs will be asked to fill in a second questionnaire after 12 to 18 months. In this way, we will explore which views and possible changes in health services persist over time. As the questionnaires will be anonymous, the comparison will be made on an aggregated level.

The GPs who participated in the first survey will also be asked to cooperate in the patient survey. Those who indicate an interest on the response form will be contacted again with further information on the proceedings and will be asked to consent into participating in the study. From a previous study (not yet published), we expect about 50 to 100 GPs to take part in this portion of the study. Participating GPs may indicate whether they expect to successfully distribute questionnaires for 50 or 100 patients during the standardized study period of four weeks. Questionnaires will be sent to the practices accordingly to be distributed among patients who sit in the waiting room. Patients will be provided with information on the study, asked to fill in the questionnaire anonymously, and to place it in a pre-prepared box. After the given study period, the practice team will send back the questionnaires using a prepaid envelope.

Inclusion criteria are:

At least 18 years old or moreAble to read and fill out a German questionnaire

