## Introduction

Primary care plays a crucial role during the COVID-19 pandemic [1, 2].

While hospital care and the concern around potential insufficient intensive care resources were very much a focus in the earlier stages of the pandemic, it was the GP practices who usually (and, again, were) the first point of contact for the patients. Practices often had to decide who needed hospital care; they also provided and monitored patients with COVID-19 at home while providing continuous care for all other patients [3–5].

In Germany, 80 to 85 percent of the patients suffering from Covid-19 received medical care in the ambulatory care sector [6]. Important characteristics of the German health care system as a framework for GP practice organization are described in Box 1.

Box 1. Characteristics of the German health care system as a framework for GP practice organization
Generally
lack of a gatekeeping system;important role of self-governing bodies [7, 8].
General practitioners
are on average responsible for 2,000 inhabitants;see on average 242 patients per week, with an average consultation time of 7.6 minutes;are usually self-employed and work in large part in a single-handed practice;usually rely on a personal communication infrastructure with colleagues, other specialists, and nursing facilities;largely decide autonomously about staff, working hours, and the organization of their practices [7, 9].
Medical practice assistants
(also called health care assistants, or “Medizinische Fachangestellte” in German)work under the legal responsibility of the GPs;go through a three-year vocational training program;are qualified for office and management duties as well as basic clinical tasks, such as measuring blood pressure and taking blood samples;may take over additional tasks including injections, vaccinations, or home visits, according to the “Agreement on the delegation of medical services to non-medical staff in ambulatory healthcare” [10–12].

The pandemic resulted in several spontaneous and unsystematic changes in the supply and uptake of health care services, affecting general practitioners (GPs), medical practice assistants (MPAs), and their patients [13, 14].

The idea for the study protocol presented here was developed in a practice advisory board meeting of the practice-based research network RESPoNsE (for details on RESPoNsE, see Box 2).

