### Data analysis

Data from the returned self-reported questionnaires will be entered manually into a Microsoft Excel spreadsheet and imported into IBM SPSS software (V.28) for data cleaning and analyses. Descriptive statistics (such as frequencies and proportions), summary statistics (such as means with standard deviations or median with interquartile range, as appropriate), and the number of missing values for each variable will be reported. Missing values will not be imputed.

The association of selected demographic and professional characteristics regarding respondents´ views and experiences will be verified with the chi-square test of independence for categorical variables and parametric or non-parametric tests for continuous variables, depending on the distribution. A comparison of GPs´and MPAs´ answers will be performed accordingly. The threshold for significance will be set at 0.05. Multivariate regression analyses will be applied to selected items where appropriate.

Qualitative data from the interviews and focus groups will be analyzed using thematic analyses based on a combined inductive and deductive approach [68]. Data analysis and coding will be facilitated by using the software MAXQDA 2022, release 22.1.1. One author of the multidisciplinary research team will start categorizing and coding the first interviews and develop a coding framework, which then will be discussed with the other members of the research team before being applied to the proceeding interviews.

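### The service-frequency scale cannot separate a maintained service from one never offered, so 'no change' cannot be read as maintained supply

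*Protocol article*

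**What the plan says.** Under Quantitatively: Surveys, the protocol article states that, apart from demographics, "all the other items are designed on a five-point Likert scale", with 'don't know' added where appropriate. For the block on changes in service frequency, Table 3 prints the answer options as "Much less frequent–less frequent–no change–more frequent–much more frequent–don´t know". Among the services rated it names "virtually delivered care by use of video or telephone, home visits, routine checks, vaccinations other than Covid-19". The example item reads "How has the frequency for the following service for non-Covid-19 related conditions changed during the pandemic", with home visits as the service. No 'not offered' answer is listed, and no item on whether the practice provides the service at all.

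Outcomes defines the primary outcome in words: "The primary outcome is that the views of GPs, MPAs, and patients be obtained, on the supply and utilization of health services". Among its aspects are underuse or undersupply of care and "unanticipated benefits like improvement of organizational matters and use of virtually-delivered care". Data analysis plans "Descriptive statistics (such as frequencies and proportions), summary statistics" for the questionnaire items. Missing values are counted and not imputed. How 'don't know' enters the denominators is not stated.

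Study status says that the GP and MPA survey began in March 2022 and will be repeated in 2023. When the article was written, the patient survey was still to be prepared.

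**The concern.** The block asks about change without asking about the starting level. Zero home visits before and zero during the pandemic is 'no change'; a full programme kept going is also 'no change'. For a study of undersupply and of the use of virtual care, these are opposite situations, and the answer does not tell them apart.

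Practices can be expected to differ in what they offer: Box 1 of the Introduction says that GPs "largely decide autonomously about staff, working hours, and the organization of their practices". A table showing a large 'no change' share for home visits could easily be taken to mean that supply held up, when part of that share never had a supply to hold up. Because the questionnaires are anonymous and the two waves are compared only in aggregate, never-providers cannot be identified afterwards by linking records.

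**Working it through.** The article states no figure on this point, so there is nothing to reproduce. The calculation below is an illustration, and every input to it is assumed.

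**Inputs**
- q: share of respondents whose practice never provided the service. Not given; 5% to 50% tried.
- c: share of those who tick 'no change'. The rest tick 'don't know' or leave the row blank and are excluded. Not given; 0, 0.5 and 1 tried.
- D, S, M: shares of 'less', 'no change' and 'more' among providers. Not given; assumed 50/40/10% for home visits and 5/25/70% for video.

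**Formulas**
- Reported 'less' = (1−q)D / [(1−q) + qc]
- Reported 'more' = (1−q)M / [(1−q) + qc]
- Never-providers within 'no change' = qc / [(1−q)S + qc]

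**Worked case, q = 5%, c = 1.** The denominator is 0.95 + 0.05 = 1.
- Home visits: reported 'less' = 0.95 × 0.50 = 47.5%, against 50% among providers, a shift of 2.5 points. Never-providers within 'no change' = 0.05 / (0.95 × 0.40 + 0.05) = 11.6%.
- Video: reported 'more' = 0.95 × 0.70 = 66.5%, against 70%, a shift of 3.5 points. Never-providers within 'no change' = 0.05 / (0.95 × 0.25 + 0.05) = 17.4%.

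**Range**

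| q | c | Home visits 'less' | Never-providers in 'no change' | Video 'more' | Never-providers in 'no change' |
|---|---|---|---|---|---|
| any | 0 | 50% | 0% | 70% | 0% |
| 5% | 1 | 47.5% | 11.6% | 66.5% | 17.4% |
| 10% | 1 | 45% | 21.7% | 63% | 30.8% |
| 20% | 0.5 | 44.4% | 23.8% | 62.2% | 33.3% |
| 20% | 1 | 40% | 38.5% | 56% | 50% |
| 30% | 1 | 35% | 51.7% | 49% | 63.2% |
| 50% | 1 | 25% | 71.4% | 35% | 80% |

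**Effect of the denominator rule.** The c = 0 row shows no distortion only because 'don't know' and blank answers are excluded. If they are kept in the denominator, reported 'less' and 'more' become (1−q)D and (1−q)M, the same values as with c = 1. The missing rule therefore matters. Even when they are excluded, never-providers who tick 'don't know' are mixed with respondents who cannot judge, so the share not offering the service is still unknown.

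**The case against.** A reader might infer that a never-providing practice necessarily scores 'no change' and that the primary outcome is distorted. The article does not support that.

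- Nothing says how such a respondent answers. 'Don't know' or a blank row is equally open.
- No primary-outcome proportion is defined. The outcome is the views of three groups, gathered also through a patient survey and interviews, in a study called explorative. Another block asks about quality of care and practice visits for chronically ill patients.
- As shares of all respondents, reported increases and decreases are correct. The article nowhere promises provider-only proportions or says that 'no change' will be read as care maintained.
- It is also tempting to say that the planned tests by practice location could turn significant falsely. With an assumed 70% increase among providers and 20% versus 40% never-providers, two locations would show 0.7 × 0.8 = 56% and 0.7 × 0.6 = 42%. That is a real difference in the share of respondents reporting more use. It misleads only if read as a difference among providers.
- Table 3 lists video and telephone together. If they form one item, a practice must offer neither to be a never-provider, and there may be few of those.
- The questionnaire was piloted with the practice advisory board. The mixed-methods section plans a critical look at the quantitative measures, and interviews may reveal misread questions.

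All of this stands as a limit on the size and reach of the point. It does not remove the ambiguity: the scale is printed in full, 'don't know' is the only supplement named, and neither piloting nor a small set of interviews can divide the 'no change' answers afterwards. The full questionnaires (S2 and S3 Files) were not available for this review; a provision item there would settle the matter, but the article describes none.

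**Conclusion.** The point holds as a limit on interpretation. On the scale as printed, 'no change' covers both a service kept up and a service never offered, so it cannot stand as evidence of maintained supply. The 'less' and 'more' proportions describe all respondents, not providers.

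The effect may be nil, if never-providers tick 'don't know' or skip the row and are excluded. It is about 2.5 to 3.5 points at a 5% never-provider share if all tick 'no change', and it grows with that share. These figures rest on the assumed 50% decrease in home visits and 70% increase in video among providers, and on assumed never-provider shares; the article supplies none of them. The point warrants a change because the block bears on undersupply and virtual care, both named under the primary outcome, and because the repeat survey and the patient questionnaire could still be adapted when the article was written.

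**What to change.** 1. In the 2023 repeat survey, leave the frequency scale as it is. After that block, so that the wave-1 question order is preserved, add one tick per service: offered before the pandemic, newly introduced during it, or not offered.
2. Report less, same and more for all respondents on the unchanged scale for the wave-to-wave comparison. For wave 2, report them also among providers, with the share not offering the service alongside.
3. Report 'don't know' as its own category, with the same stated denominator rule in both waves.
4. Label the wave-1 category 'no change or service not offered', and do not interpret it as maintained provision.
5. In any service-change items of the patient questionnaire, include a 'did not use / not applicable' answer.

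A separate tick is better than a new option inside the scale. Folding 'not offered' back into 'no change' would restore comparability only if every wave-1 never-provider had ticked 'no change', which cannot be checked.

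The cost is a slightly longer questionnaire and a few extra lines in the results tables. Provider-only results will exist for wave 2 alone.
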